## Abstract

**Background:**

Assessment of co-morbid personality disorders in substance use disorders may lead to important insights concerning individual patients. However, little is known about the potential value of routine personality disorder assessment in a clinical context.

**Methods:**

Patients are adults with past-year substance dependence seeking treatment at a centralized intake unit for substance abusers in the City of Copenhagen. A randomized controlled trial of assessment of personality disorders and individual feedback vs. a general life situation interview. Patients are followed at 3 and 6 months post-treatment

**Discussion:**

If routine personality assessment improves outcomes of substance abuse treatment, the clinical implication is to increase the use of personality disorder assessment in substance abuse treatment settings.

**Trial registration:**

Current controlled trials ISRCTN39851689

## Background

Substance use disorders and personality disorders often co-occur [1,2]. Patients with personality disorders are commonly seen in treatment programs for substance abuse, consume a disproportionate amount of staff time, and are more likely to drop out from substance abuse treatment interventions [3,4].

At the same time, therapists and other professionals tend to react negatively to patients with personality disorders at an emotional level [5], this is especially the case with cluster B (dramatic/erratic) personality disorders [6].

Even if patients with personality disorders benefit from treatment, they often remain more symptomatic than patients without personality disorders, and remain at a lower level of functioning [7,8].

Therefore, treatment that meets the needs of patients with substance abuse and personality disorders is needed. Recently, some studies have shown that integrated treatment for personality disorders and substance abuse may be superior to treatment that focuses solely on substance abuse treatment [9-11].

This randomized experimental study is designed to assess whether systematic assessment of personality disorders improves outcomes, vs. assessment of Axis I disorders alone.

The objective of this study is to estimate the effect of routine assessment of co-morbid axis II disorders in a centralized intake unit for substance use disorders.

## Method

### Design

The study is a randomized experimental trial comparing assessment of Axis I disorders alone with assessment of both Axis I disorders and Axis II disorders. For both treatment conditions, patients are given feedback about the results of assessment and offered the opportunity to have their key-worker receive the same feedback.

### Participants/setting

Participants are adults seeking treatment for a substance use related disorder at the Central Intake Unit (CIU) in Copenhagen, Denmark ([name]).

### Referral and recruitment

Patients are recruited by caseworkers. The management of the intake unit and the management of the centre have instructed all caseworkers to ask all new referrals or those referred for a change in treatment to participate in the study.

Caseworkers inform patients that the study concerns assessment of psychological problems, behaviour and other disorders, and that patients will be randomly assigned to one of two types of interviews. The primary interviewer later gives detailed information about the study procedure.

### Inclusion criteria

To be eligible for the study, patients must satisfy the following criteria:

• Be at least 18 years of age.

• Not currently be psychotic or have a known diagnosis of schizophrenia excluding patients from treatment at the intake unit.

• Not currently be involved in an ongoing treatment for a drug or alcohol problem. Patients who are currently involved in treatment for alcohol or drug abuse will, however, not be referred to the CIU.

• Have past-year substance dependence, as indicated by a score on the SDS of 3 or more for either alcohol or drugs.

• Speak Danish or English fluently.

• Give informed consent.

The assessment and feedback takes place in the first three weeks of treatment.

Table 1 gives an overview of the interviews and questionnaires conducted at the different assessment times. Figure 1 represents the research procedure schematically. Figure 2 contains the expected participant flow.

**Figure 1 F1:**
[figure not shown]
Flowchart of the process from information to follow-up.

**Figure 2 F2:**
[figure not shown]
Flowchart of participants.

**Table 1 T1:** Instruments at different assessment moments

	Baseline	Follow-up	Follow-up
Interview:			
SAPAS [22, 23]	*	*	*
ASRS [14]	*	*	*
K6 [32]	*	*	*
OTI [15]	*	*	*
SDS – alcohol [21]	*	*	*
SDS – drugs [21]	*	*	*
WAI [29]		*	
Ratings of the feedback procedure – VAS		*	
Clinician rated:			
CGI-externalizing [23]		*	*
CGI-substance use [23]		*	*
GAF [23]		*	*
WAI [29]		*	

**Notes**: *SAPAS*: Standardised Assessment of Personality – Abbreviated Scale. *ASRS*: Adult ADHD Self-Report Scale. *K6*: Kessler 6. *OTI*: Opiate Treatment Index. *SDS*: Severity of Dependence Scale. *WAI*: Working Alliance Inventory. *VAS*: Visual analogue scales. *CGI*: Clinical Global Impression. *GAF*: Global Assessment of Functioning.

### Outcome criteria

The main outcome criterion will be the following: Improvement in at least one of the following areas, described as a 30% decline in score, with no concurrent deterioration in any area: global functioning, as measured by the Work and Social Adjustment Scale [12]; psychiatric symptoms, as measured by the Kessler 6+ [13,14]; substance use, as measured by the Opiate Treatment Index drug use indicator [15]; treatment engagement, as measured by treatment staff, using the treatment engagement scale from DATOS [16].

Secondary outcome criteria will be

• Retention in treatment, defined as being retained in the same treatment that patients were first referred to after their contact with the intake unit at 3 and 6 months follow-up, or having completed that treatment as planned.

• Understanding of one's own personality and the impact that personality has on others, as rated by an independent interviewer [17].

• Readiness to change dysfunctional behaviour, work with emotional problems, change illicit drug use, and change alcohol use, as measured by brief 4-item questions, adapted from the smoking cessation literature [18].

Outcome criteria will be assessed at 3 and 6 months follow-up.

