### Outcome evaluation

A single measure of outcome will be used as the primary outcome measure: The proportion of areas in which a 30% reduction occurred at each follow-up wave (K6, WSAS, and OTI substance use). This measure can theoretically range from -3 (deterioration in all areas) to +3 (improvement in all areas.

The data will be analyzed with mixed effects ordinal regression, using baseline values of the three outcome measures as covariates [30].

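### The primary outcome is defined twice in incompatible ways: a yes/no criterion over four areas in which any deterioration disqualifies, and a −3 to +3 score over three areas in which deterioration only offsets improvement

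*Protocol article*

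**What the plan says.** Two sections of the protocol article each name a primary outcome.

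- **Outcome criteria** opens with "The main outcome criterion will be the following" and gives a yes/no rule: "Improvement in at least one of the following areas, described as a 30% decline in score, with no concurrent deterioration in any area". Four areas follow: global functioning (WSAS), psychiatric symptoms (Kessler 6+), substance use (OTI drug use indicator) and treatment engagement rated by staff (DATOS scale).
- **Outcome evaluation** states: "A single measure of outcome will be used as the primary outcome measure". It describes this measure as "The proportion of areas in which a 30% reduction occurred at each follow-up wave (K6, WSAS, and OTI substance use"), which is three areas, and adds: "This measure can theoretically range from -3 (deterioration in all areas) to +3" for improvement in all of them. The analysis is mixed effects ordinal regression, adjusted for the baseline values of three outcome measures.

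Both definitions apply at the 3- and 6-month follow-ups. Nothing in the article ranks one above the other or links them.

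**The concern.** The definitions differ in three respects: the areas covered (four or three), the type of variable (yes/no or ordinal score), and the role of deterioration (it disqualifies in one and is offset by improvement in the other). The second definition is also at odds with itself, because a proportion of areas with a 30% reduction lies between 0 and 1 and cannot reach −3.

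The trial exists to say whether personality disorder assessment improves outcome. With two published primary outcomes, either could be presented as the planned one once results are known, and a reader could not tell which result was meant to answer the question.

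**Working it through.** **Inputs.** The areas, rules and range come from the two sections above. The article gives no rates of improvement or deterioration and no correlation between areas, so those below are assumptions.

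**Step 1: reproduce the stated range.** Code each area +1 (improved), 0 (unchanged) or −1 (deteriorated).
- Sum over three areas: minimum 3 × (−1) = −3, maximum 3 × (+1) = +3. This matches the article.
- Sum over four areas: −4 to +4. No match.
- Proportion of areas improved: 0 to 1. No match.

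The stated range therefore implies a net count over three areas, improved minus deteriorated.

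**Step 2: apply both definitions to the same patient.** The criterion needs at least one +1 and no −1 over four areas. The score is the sum of WSAS, K6 and OTI.

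| WSAS, K6, OTI | Engagement | Score | Four-area criterion |
|---|---|---|---|
| all improved | worse | +3 | not met |
| two improved, one worse | any | +1 | not met |
| one improved, two unchanged | unchanged | +1 | met |
| all unchanged | improved | 0 | met |

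The first and last rows are ranked in opposite order by the two definitions, and seeing this needs no cut on the score. The second and third rows share a score of +1 but differ on the criterion.

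**Step 3: count patterns.** Of the 3⁴ = 81 four-area patterns, a score of +1 covers 18, of which 6 meet the criterion and 12 do not. If a score above 0 is taken as net improvement (an assumed cut, since the article sets none), 16 patterns score above 0 but fail the criterion, and 1 meets it with a score of 0. That makes 17 in conflict. With engagement removed, 7 of the 3³ = 27 patterns meet the criterion, 10 score above 0, and the 3 in conflict are those with two areas improved and one worse. The deterioration rule alone is enough to produce conflict.

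**Step 4: illustrate the share of patients.** Let p, d and u = 1 − p − d be the probabilities of improvement, deterioration and no change in each area, with areas independent.
- Criterion met (four areas): (1 − d)⁴ − u⁴
- Score above 0: p³ + 3p²u + 3p²d + 3pu²
- Disagreement: P(score above 0) − (1 − d)[(1 − d)³ − u³] + pu³

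Example with p = 0.4, d = 0.2, u = 0.4:
- Criterion met: 0.4096 − 0.0256 = 0.384.
- Score above 0: 0.064 + 0.192 + 0.096 + 0.192 = 0.544.
- Disagreement: 0.544 − 0.8 × 0.448 + 0.4 × 0.064 = 0.211.

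| p, d | Criterion met | Score above 0 | Disagreement |
|---|---|---|---|
| 0.50, 0.15 | 51% | 68% | 22.0% |
| 0.45, 0.20 | 39% | 59% | 23.5% |
| 0.40, 0.25 | 30% | 50% | 23.2% |
| 0.35, 0.25 | 29% | 45% | 20.4% |
| 0.30, 0.10 | 53% | 54% | 14.3% |

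**Step 5: relax independence.** The areas are measured on the same patient, so their changes are plausibly correlated. A Gaussian copula with the first four pairs gives disagreement of 13–15% at correlation 0.3, 9–10% at 0.5 and 5–6% at 0.7. With three areas in both definitions, the independent figure is 3p²d = 9–12%, falling to 5–7%, 3–4% and about 1%.

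**The case against.** The strongest reply is that the article leans towards the three-area score. Only that version comes with a named analysis, the model is ordinal, and the covariates are three baseline measures. Neither Table 1 nor the instruments listed under Follow-up procedure include an engagement scale. This stands in part. It makes the choice less open than two equal candidates would be, and it is the reason to prefer the score in the correction. It does not remove the conflict, because the four-area criterion is still labelled the main outcome. Nor is Table 1 a sure guide, since it also omits WSAS, which both definitions use.

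A second reply is that such details belong in a full protocol or analysis plan. That would excuse an omission, but this is a contradiction between two statements in the published text. It does apply to the deterioration threshold. Neither section gives one, but an article may leave it to the fuller document, so its absence is not counted here as an error.

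Three stronger readings are tempting and not supported:
- *Type I error control is broken.* That would require an actual choice made on the results. The text only leaves room for one.
- *The definitions misclassify a fifth to a quarter of patients.* That figure needs independent areas, rates that the article does not give, and a success cut that the score does not have.
- *The two outcomes differ in power by a known amount.* The article gives no sample size, significance level or rates, so no power can be computed.

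**Conclusion.** The point holds as a contradiction in the text. The two primary definitions differ in areas, type of variable and treatment of deterioration, and the second misnames its own measure as a proportion. The +3 patient who fails the criterion shows the conflict without any assumption about rates or cut-offs.

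The share of patients affected is illustrative only. With an assumed cut of score above 0 and the first four assumed pairs of rates, it is about 20–24% under independence and about 5–15% at correlations between 0.7 and 0.3. It is lower with lower rates of change. The conclusion does not rest on these figures. The consequence is an ambiguous primary result and room to select it after the fact. That warrants correction before unblinding.

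**What to change.** Keep one primary outcome and word it identically under Outcome criteria and Outcome evaluation. The three-area score is the natural choice because it matches the stated range, the ordinal model and the three baseline covariates. Suggested wording: *net number of areas (K6, WSAS, OTI substance use) improved minus deteriorated, range −3 to +3, at each follow-up wave*. Delete the word proportion, and label the four-area responder criterion secondary.

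The trialists should set the deterioration threshold. A 30% worsening, mirroring the improvement rule, is one option, but the article does not state it.

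The cost is a change of wording, provided that WSAS is collected at baseline. This needs confirming: Table 1 and the instrument list under Baseline interview omit it, and only Follow-up procedure implies it, by including WSAS among the elements shared with baseline. If baseline WSAS was not taken, neither definition can be computed for that area, and the problem is no longer one of wording alone.

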### Follow-up procedure

Trained interviewers will make contact with study participants before randomization, but after intake interview. Interviewers will be blinded to randomization status. The follow-up interview will contain the same elements as the baseline interview (i.e., the K6, the ASRS, the WSAS, the OTI, and the SDS). Also, patients will be asked to rate the value of the feedback procedure on visual analogue scales representing the skills of the interviewer (on a line ranging from "extremely unskilled" to "extremely skilled"), his knowledge (from very little knowledge, to highly knowledgeable), his degree of interest in the patient, his understanding of the patient, the value of the feedback for the treatment, the value of the treatment for the patient, how much thought the patient has given the feedback, and how much work he has done in regard to the issues discussed in the feedback.

Finally, the patient is asked to rate his alliance with the caseworker using the Working alliance inventory, patient version [29].

At each interview point, the caseworker is asked to rate the patient using the clinical global impression scale with anchor points for alcohol and drug abuse [23], externalizing behaviour [23], and GAF [23], and to complete the Working Alliance Inventory, clinician version [29].

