### Data handling and record keeping

Patient information will only be accessible to the research team. All data will be link-anonymised so that no patient identifying information will be kept with raw data. All files will be kept with the local research teams in a locked and secure cabinet. Electronic data will be stored on a central computer at the research centre.

A personal feedback letter will be given to the patient, in which the patient appears only with his or her first letter. If the patient agrees that the information in the personal feedback should be shared with the caseworker, then the same letter will be given to the caseworker. Raw data will, however, only be kept and stored by the Centre for Alcohol and Drug Research.

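### Treatment engagement is a fourth area of the main outcome in one section and absent from the primary measure in another; its improvement rule and missing rating schedule do not fit it

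*Protocol article*

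**What the plan says.** The Outcome criteria section sets one rule for the main outcome: "Improvement in at least one of the following areas, described as a 30% decline in score, with no concurrent deterioration in any area". Four areas follow: global functioning (WSAS), psychiatric symptoms (Kessler 6+), substance use (OTI), and "treatment engagement, as measured by treatment staff, using the treatment engagement scale from DATOS". No separate rule is given for the fourth. On timing, the section says "Outcome criteria will be assessed at 3 and 6 months follow-up".

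The Outcome evaluation section then defines one primary measure from 30% reductions in K6, WSAS and OTI substance use. It gives the range as -3 to +3 and adjusts for the baseline values of those three measures. Engagement does not appear.

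Table 1 ("Instruments at different assessment moments") lists CGI, GAF and WAI as clinician ratings, marked only at follow-up. The Follow-up procedure section says "At each interview point, the caseworker is asked to rate the patient using the clinical global impression scale", together with GAF and the WAI. Neither names an engagement scale, nor does the instrument list under Baseline interview.

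On who learns what, the Data handling section says that if the patient agrees to share the feedback, "then the same letter will be given to the caseworker".

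**The concern.** The rule suits symptom, impairment and drug-use scores, where lower is better. Engagement would normally be scored the other way. Read literally, a patient who disengages could satisfy the improvement criterion, and one who engages more could be classed as deteriorated and lose a success earned elsewhere.

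A percentage change also needs a starting value, and the article shows no engagement rating at any visit. Finally, the raters are treatment staff, for whom no blinding is stated and some of whom may have read the feedback.

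What is at stake is the definition of the main outcome. While both definitions stand, it is unclear whether engagement counts, and the choice could be made after the data are seen.

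**Working it through.** **1. Which definition does the stated range fit?** Code each area -1 (deteriorated), 0 or +1 (improved) and sum.

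- Three areas (K6, WSAS, OTI): minimum 3 × (-1) = -3, maximum 3 × (+1) = +3. This reproduces the stated range.
- Four areas (with engagement): -4 to +4. This does not match.

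The three baseline covariates agree with the three-area version. Outcome evaluation therefore excludes engagement in its list, its range and its covariates, while Outcome criteria includes it.

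**2. Is an engagement rating scheduled?**

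| Place in the article | Staff or caseworker ratings named | Engagement scale |
|---|---|---|
| Baseline interview | none | not listed |
| Table 1 | CGI, GAF, WAI (follow-up only) | not listed |
| Follow-up procedure | CGI, GAF, WAI | not listed |

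A 30% change is (baseline - follow-up) / baseline ≥ 0.30. Neither term is scheduled for engagement, so the criterion cannot be evaluated from the data that the article says will be collected.

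**3. What does the direction of scoring do?** Assume that higher means more engaged. This illustration uses assumed rates and independent areas, and it applies only to the four-area definition. With b the probability of improvement and w the probability of deterioration in each area, the responder probability is

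R = ∏(1 - w) - ∏(1 - b - w).

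Let the other three areas each have b = 0.30 and w = 0.10, so that 0.90³ = 0.729 and 0.60³ = 0.216. Let engagement fall in 10% of both arms, and rise in 20% of controls and 40% of the experimental arm.

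- A rise counts as improvement: control 0.729 × 0.90 - 0.216 × 0.70 = 0.505; experimental 0.729 × 0.90 - 0.216 × 0.50 = 0.548. Difference +4.3 points.
- A fall counts as improvement and a rise as deterioration: control 0.729 × 0.80 - 0.216 × 0.70 = 0.432; experimental 0.729 × 0.60 - 0.216 × 0.50 = 0.329. Difference -10.3 points.
- A fall counts as improvement and a rise counts as nothing: both arms 0.729 - 0.216 × 0.90 = 0.535. Difference 0.

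With b = 0.40 and w = 0.15 in the other areas (0.85³ = 0.614, 0.45³ = 0.091), the first two cases give 0.489 v 0.507 (+1.8 points) and 0.428 v 0.323 (-10.5 points).

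Under these assumptions, the literal rule loses a real gain in engagement or reverses its sign. The reversal needs the further assumption that a rise is deterioration, which the article does not define.

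**4. Who is blinded?** Randomization and blinding covers the interviewer at baseline. Follow-up procedure and Discussion cover the follow-up interviewers. Discussion adds that patients do not know whether their condition is labelled experimental or control. Treatment staff are not mentioned. Design and Data handling make sharing with the key-worker or caseworker depend on the patient's agreement; Ethical approval says without condition that caseworkers get feedback and advice. A route to knowledge of the arm therefore exists, but how many raters it reaches is not stated.

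**The case against.** The strongest reply is that Outcome evaluation already fixes a single primary measure without engagement. Under that measure, a disengaging patient cannot count as a success through this route. This stands and limits the harm. It does not remove the contradiction, because Outcome criteria still calls its four-area version the main criterion.

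Table 1 is also incomplete. It and the baseline instrument list both omit the WSAS, which Follow-up procedure says belongs to the baseline interview. So a reader who infers that no baseline engagement score exists goes too far: the article shows only that none is scheduled. Nor does it follow that engagement could not be rated early, since Inclusion criteria places assessment and feedback within three weeks of treatment starting. Still, the WSAS is placed in the interviews by another section, and engagement is not.

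The scoring direction of the DATOS scale is not in the article. If lower means more engaged, the direction problem disappears and the rest remains.

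A reader might infer that the staff ratings are biased by arm, because the Background says that "therapists and other professionals tend to react negatively to patients with personality disorders at an emotional level". The document does not establish this. That sentence concerns patients with the disorders, whom randomisation should balance, not a reaction to a label. Sharing the letter depends on consent under Design and Data handling, and the raters are not identified as its recipients. The SAPAS is given at baseline in both arms, and the article does not say that control letters are silent on personality. Feedback to caseworkers is also part of the intervention, so informed staff are inherent in the design. What stands is that bias is possible and no safeguard is described.

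It is also tempting to size the problem by how far a fourth area lowers the responder rate. Any fourth independent area with the same rates would lower it equally under the no-deterioration clause, even one that is well scored and blinded, so that figure would not measure this defect.

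**Conclusion.** The main outcome as written in Outcome criteria is wrong for engagement and contradicts Outcome evaluation. Two findings need no outside assumption: the sections name four and three areas, with the stated range fitting three, and the article schedules no engagement rating from which a 30% change could be computed. One is conditional: if higher means more engaged, the rule counts disengagement as improvement. One is a possibility only: rating bias by arm, which the document gives no basis for quantifying. The responder differences shown above rest on assumed rates and independence and are not estimates for this trial.

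The point should be settled before analysis because it concerns the main outcome. It does not show that the three-area analysis is biased, or that engagement could never be a valid outcome.

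**What to change.** Delete treatment engagement from the main outcome in Outcome criteria, so that its areas are the K6, WSAS and OTI used in Outcome evaluation. List engagement as a secondary outcome, analysed as the follow-up score itself and not as a percentage change. State its scoring direction, add its rating visits to Table 1 and Follow-up procedure, and say that it is rated by treatment staff who are not blinded.

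The cost is a change of wording. The main outcome loses one area, which Outcome evaluation already assumes.
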